## 8f. Data management

### *8f i. Study identification numbers and linking of records*

Upon consenting to participate in the study, each subject will be assigned a random study identification number. This will be a five-digit number in which the first digit indicates the study track (1 or 2). The remaining four digits will be a randomly generated number that does not provide any identifying information.

A password-protected, encrypted linking file will be created in Excel to link study identification numbers to subjects' names, dates of birth, national identity numbers, and clinic file numbers. These fields are needed to ensure that study ID numbers can be correctly matched to the identification numbers used in the site's electronic medical record system (MRS) where patient records are kept after ART initiation. When a subject has been matched to a record in the MRS, the MRS record number will also be added to the linking file. The linking file will be a separate document from any other study files. Access to the linking file will be limited to the study team, and the file will be stored in a secure location separate from the study database.

#### *8f ii. Data management and storage*

Study specific data will be captured on site on the paper case report form described above. These forms will be scanned on site by study staff. Scanned files will immediately be password protected and encrypted. Protected and encrypted files will then be transferred at the end of each day or at weekly intervals to an access-limited Dropbox folder and then immediately downloaded to the study team's secure office network. Upon confirmation of receipt of the scanned files, the original pdfs will be deleted from the study computer on site. Original paper case report forms will be physically transferred to the study office once a week and stored in a secure cabinet. (Source documentation such as printouts of results of laboratory tests will remain at the study site and filed following the site's usual record-keeping procedures. Source documents will never be removed from the study site.)

Study-specific data from case report forms will be entered and managed using Research Electronic Data Capture (REDCap, <http://project-redcap.org>), a web-based tool for electronic collection and management of research data. The REDCap system provides a secure, web-based platform for data entry that allows real time monitoring, querying, and quality control of data by an off-site data manager. It allows access to data to be assigned and restricted to individual study staff as needed and creates audit trails to monitor appropriate access. It is supported by the Boston University IT office (<https://redcap.bumc.bu.edu/>). It has previously been used successfully in South Africa, where the University of the Witwatersrand is a REDCap Consortium partner.

The study's lead data analyst will review the study database in REDCap on a daily basis during the pilot phase and on a weekly basis (or more frequently) thereafter. The data analyst will run data cleaning routines regularly and generate queries to return to the site-based staff for resolution as needed.

Medical record data for study subjects will be downloaded from the site's existing electronic medical record system, as described above. Records in this system are created only when patients initiate ART, and thus do not capture pre-ART care (HIV tests, monitoring CD4 counts, etc.). The lead data analyst will be responsible for ensuring that study identification numbers are correctly matched to the record numbers in the MRS. In instances where the data analyst cannot match a study ID number to an electronic medical record number using only the fields in the study linking file, a query will be sent to the on-site study staff, who will access the clinic's paper-based patient files to determine whether the subject ever initiated ART and, if so, locate the correct MRS number.

For subjects in the standard group, eligibility for study enrollment can only be determined once treatment eligibility is established by CD4 count or other criterion. For these subjects, the study team will review the site's paper-based patient files on a monthly basis to determine whether and when the subject has been found eligible for treatment and if treatment has been initiated. This information will be entered onto case report forms and captured in the REDCap database as described above.

A note or tab indicating that a patient is a participant in the study will be attached to the cover of each subject's paper medical record at the study site, to assist site and study staff in locating study subjects' files should this be necessary and to ensure that site staff are aware of which patients are study participants.

#### *8f iii. Data quality assurance*

As case report forms are completed, they will be quality-checked by a member of the study team to ensure missing or illogical data are corrected. If any changes to paper forms are made, the original data will be left and crossed out, and the corrected data will be written next to it with a signature and date of the person who made the change. As described above, the lead data analyst will review subject records in REDCap on a weekly basis or more frequently if needed so that queries can be sent to the on-site staff promptly. The lead data analyst will also be responsible for data cleaning and management. Data completeness and quality will also be reviewed on a monthly basis by the investigators. Monthly updates on study enrollment numbers and randomization allocation will be sent by the analyst to the PI and co-investigators for monitoring progress.

#### *8f iv. Aggregate statistics*

Subjects who consent to study participation but are not eligible for ART and those who are found to be study ineligible for any other reason will not be enrolled in the study, as explained above. These subjects' ineligibility for the study will be confirmed by the lead data analyst. Data already collected for these subjects will be used to compile aggregate information on a monthly basis regarding patients at this site who are not eligible for treatment (e.g. average age and average CD4 count of patients who test HIV-positive). Individual data will be destroyed at the end of each month following compilation of the monthly aggregate statistics. Source documents for any test results (CD4 count, TB test result) generated during screening procedures will be retained in the study clinic's file for the patient.

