### 3b. Reasons for high rate of loss

Although studies in different parts of Africa have identified several psycho-social and structural reasons for failing to start ART, one major barrier is clearly the daunting number of steps required between receiving an HIV diagnosis and obtaining the first dose of ARVs. In South Africa, these steps include:

- 1) Confirmation of treatment eligibility (CD4 count);
- 2) TB diagnosis and treatment initiation if indicated;
- 3) Hemoglobin, liver function, pregnancy, and creatinine clearance tests;
- 4) General medical exam; and
- 5) Several (typically 3-4) wellness/treatment readiness/adherence sessions.

Except for the sickest patients, these activities usually require several clinic visits and a 1-2 month interval to complete even if patients adhere to the clinic's schedule. Standard laboratory technologies and procedures in use throughout sub-Saharan Africa typically require patients to make two clinic visits per diagnostic test, one to provide a sample and another to receive results. As laboratories have struggled to keep pace with the expansion of treatment programs, the time interval between these two visits has increased in many locations. In the research team's experience in South Africa, completion of a baseline CD4 count for determination of treatment eligibility can take between 2 days and 4 weeks, depending on the location of the lab, the time required to process the sample, and the promptness of the patient's return. Similarly, diagnosis of pulmonary TB requires anywhere from 2 days to 6 weeks or longer, depending on the type of TB (smear positive or smear negative), backlog at the laboratory, and delays in communicating results to the treatment site and thence the patient. Since up to 70% of HIV patients may be considered TB suspects and require TB diagnosis even though  $< 20\%$  have TB, TB diagnosis also causes substantial delays in ART initiation and leads to high loss to follow up from both HIV and TB treatment.

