#### *6b iv. Randomization and blood draw*

After the questionnaire has been completed, subjects will be randomized to the rapid or standard groups of the study. Randomization envelopes will be generated in blocks of 6 and kept at the study site. For each enrolled subject, the study assistant will open the next envelope in sequential order, read the randomization group, and record it on the case report form.

Depending on the randomization group, the study assistant will then ask subjects in the standard group to return to the clinic nurse for a blood draw for a standard CD4 count and subjects in the rapid group to go to the study nurse for a blood draw for a rapid CD4 count. Following the blood draw, the study assistant or study nurse will inform subjects of their group assignment. Standard group subjects will be asked to proceed with a standard pre-ART care visit. The study assistant will repeat the explanation of next steps in the study, which are limited to review of medical records by the study team, and thank them for their willingness to participate in the study. The study team will have no further personal contact with patients in the standard group.

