#### *6b vi. Confirmation of treatment eligibility and study enrollment*

Under South African guidelines, ART eligibility is based primarily on CD4 count. Since a rapid CD4 count is part of the intervention for patients in the rapid group but not for those in the standard group, consent will take place before treatment eligibility is known. All subjects who meet other inclusion/exclusion criteria will be asked for consent, but only those who are treatment eligible will be enrolled in the study.

Procedures for performing a CD4 count are described below. Subjects in the rapid group will be informed as soon as their CD4 count result is available if they are eligible for treatment. Those who are not eligible on the basis of CD4 count and do not have symptoms of TB or a WHO Stage 4/3 condition will not be enrolled in the study. They will be given their CD4 count results following the clinic's standard procedures for returning laboratory results and asked to proceed with a standard pre-ART care or antenatal care visit.

Subjects in the rapid group who are eligible for treatment on the basis of CD4 count will be enrolled in the study and continue with study procedures as described below. Subjects in the rapid group who are not eligible for treatment on the basis of CD4 count but have symptoms of TB will be asked to remain in the clinic until initial TB test results are available (approximately 2 hours). Subjects who report symptoms that may indicate a Stage 4/3 condition will be examined to determine if a condition is present. Those diagnosed with TB or a Stage 4/3 condition will be enrolled in the study, while those without will be asked to proceed with a standard pre-ART care visit.

Subjects in the standard group of Track 1 will be advised to follow the standard schedule of clinic visits, which is to return to the site for their CD4 count results in 1 week. The study team will monitor CD4 count and TB test results and Stage 4/3 condition diagnoses and will enroll in the study only those who are eligible for treatment.

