#### *8f v. Destruction of data*

Data will be retained in secure study databases for 7 years following the completion of the study, including completion of all data analysis and report writing associated with the study and closing of the IRB-approved protocol. Study data sets and other electronic files containing study data will then be deleted from electronic storage locations and hard copies of study documents will be shredded.

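### Study-held individual data on randomized Track 1 subjects judged ART-ineligible are destroyed monthly, so study data cannot show whether post-randomization exclusions were comparable between arms

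*Protocol*

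**What the plan says.** Randomization comes early. Section 6b iv: "After the questionnaire has been completed, subjects will be randomized to the rapid or standard groups of the study". The CD4 blood draw follows it. Section 6b vi explains that "consent will take place before treatment eligibility is known" and that only subjects who turn out to be treatment-eligible are enrolled.

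How eligibility is found depends on the arm. In the rapid group (sections 6c i and 6c ii) it is an on-site CD4 count, a TB symptom screen with Xpert for those with symptoms, and questions about Stage 4/3 symptoms, normally on the first day. In the standard group the CD4 sample goes off site, with results in about a week (section 6d i). Section 6b vi adds: "The study team will monitor CD4 count and TB test results and Stage 4/3 condition diagnoses". Section 8f ii has the team review standard-group paper files monthly. On routine care, section 3b says that "diagnosis of pulmonary TB requires anywhere from 2 days to 6 weeks or longer".

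For subjects judged ineligible, section 8f iv first requires a check: "These subjects' ineligibility for the study will be confirmed by the lead data analyst". Monthly aggregates are then compiled, and after that: "Individual data will be destroyed at the end of each month following compilation of the monthly aggregate statistics". It also says: "Source documents for any test results (CD4 count, TB test result) generated during screening procedures will be retained in the study clinic's file". Section 8f v, with no exception for these subjects, says: "Data will be retained in secure study databases for 7 years following the completion of the study". Section 8f iii provides monthly updates on enrollment numbers and randomization allocation.

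**The concern.** Dropping ineligible people after randomization is harmless only if the dropping works the same way in both arms. Here assignment is known to staff and subjects, and the route to an eligibility decision differs by arm. Section 11b promises an intention-to-treat analysis, but in practice it covers only those who pass this arm-dependent filter.

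The direct check is to set the excluded subjects of the two arms side by side: how many, who they were, why they were excluded and when. Section 8f iv removes the study's own individual records for that check within weeks. It also leaves open when ineligibility may be declared final. If a subject is declared ineligible and a qualifying result arrives later, the questionnaire and other baseline data needed to put that person back in the analysis no longer exist. Destruction cannot be undone, so no later analysis plan can repair it.

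**Working it through.** **1. The plan's own figures.** Inputs from section 10: 50% against 70% suppressed, two-sided alpha 0.05, power 90%, 1:1 allocation, no correction; 70% of HIV-positive patients eligible; up to 600 consented and 400 enrolled.

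- n per group = [1.96·√(2·0.60·0.40) + 1.2816·√(0.50·0.50 + 0.70·0.30)]² / 0.20² = 124, as stated.
- Consented per group = 124 / 0.70 = 177.1, stated as 177 (354 in total).

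**2. Share of randomized subjects whose records would be destroyed.**

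- Planning table: 600 − 400 = 200; 200/600 = 33.3%.
- At 70% eligibility: 600 × 0.30 = 180; 180/600 = 30.0%.
- At the minimum size: 354 − 248 = 106; 106/354 = 29.9%.

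The range is therefore 30% to 33%; the upper figure is the planning maximum.

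**3. Timing.** Destruction runs on a monthly cycle. An off-site CD4 result takes about one week. Routine TB diagnosis takes from 2 days to 6 weeks (42 days) or longer, so its upper end exceeds any calendar month. Someone randomized late in a month may be only days from the first month end. The analyst's confirmation stands between a pending result and deletion, but the protocol gives it neither a minimum wait nor a list of results that must be in hand.

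**4. What survives and what does not.**

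- CD4 and TB source documents stay in the clinic's file (section 8f iv).
- Enrollment and allocation numbers are reported monthly (section 8f iii), so counts by arm may survive.
- The aggregates named as examples in section 8f iv are average age and average CD4 for patients at the site. They are not said to be by arm.
- The arm is recorded on the case report form (section 6b iv). The screening form receives the study ID and medical record number only for those enrolled (section 8b). Downloaded medical records of people not enrolled are deleted (section 12f). Whether linking-file entries for non-enrolled subjects are kept is not stated; if they are not, retained results could not readily be tied to an arm.

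**5. How far surviving counts would go.** Take 300 per arm and about 66.7% eligible on average. For a difference d between arms in the proportion judged eligible, power = Φ{[d − 1.96·√(2p̄(1−p̄)/300)] / √([p₁(1−p₁) + p₂(1−p₂)]/300)}:

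| d | power |
|---|---|
| 5 points | 25% |
| 10 points | 74% |
| 11 points | 82% |

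Counts alone would often miss a moderate imbalance, and equal counts can hide different kinds of people excluded. That is why characteristics and reasons matter.

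**6. Scale of effect, by assumption only.** Suppose 200 are enrolled in the standard arm with 100 suppressed (50%), and x eligible subjects were wrongly left out. The rate with them included lies between 100/(200+x) and (100+x)/(200+x):

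| x (assumed) | all failures | all successes |
|---|---|---|
| 5 | 48.8% | 51.2% |
| 10 | 47.6% | 52.4% |
| 20 | 45.5% | 54.5% |

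No value of x is an estimate; the documents supply none.

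**The case against.** The strongest reply is that the rule is milder than it sounds. Deletion follows confirmation by the lead data analyst, and a careful analyst would wait for pending results. Test results remain in clinic files. With sequential envelopes and monthly allocation reports, randomized minus enrolled should be recoverable by arm. Baseline predictors of the enrolled groups are compared under section 11b, where selective exclusion could also show. Any bias comes from excluding people after randomization, not from deleting their records. Given the stigma described in section 12a iii, holding little data on people outside the study is a defensible aim.

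Much of this stands. It would be wrong to infer that exclusions become wholly uncheckable by arm, or that the destroyed records are the only relevant data. It would also be wrong to infer that late eligibility arises only in the standard arm: section 6c i foresees rapid-group subjects who are ineligible on the on-site CD4 but eligible on the laboratory result, and section 6c ii foresees TB diagnoses not already made by the study nurse.

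What does not stand is that these safeguards close the gap. Nothing obliges the analyst to wait, and counts carry neither characteristics nor reasons. Confidentiality can be served by removing identifiers without destroying coded records.

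**Conclusion.** The point holds as a cheap improvement. Study-held individual data on 30% to 33% of randomized Track 1 subjects are to be destroyed monthly. Eligibility is ascertained differently by arm, and no window governs the decision that a subject is ineligible. The loss is specific: arm-linked characteristics and reasons for exclusion, and the ability to restore a late-eligible subject with baseline data. The general retention statement in section 8f v is not reconciled with this rule.

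A reader might be tempted to estimate the late-eligible subjects by taking the 30% to 33% of a 300-subject arm as those with CD4 above 350 and applying the TB prevalence of under 20% in section 3b. The documents do not support this. The 30% to 33% are ineligible on every ground, and section 5c counts TB and Stage 4/3 conditions as grounds for eligibility, so TB cases are already outside that group. Neither the share with CD4 above 350 nor TB prevalence within it is given, and many TB diagnoses would come before a month end. The number affected is unknown.

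The conclusion rests on reading the individual data in section 8f iv as including the case report form, where the arm is recorded. The section does not list the fields.

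**What to change.** In section 8f iv, replace monthly destruction with de-identification:

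- Keep one coded line for every randomized Track 1 subject: arm, site, date, age, sex, CD4 value and assay, TB and Stage 4/3 result, and reason not enrolled. Hold it for the period in section 8f v.
- Define a fixed ascertainment window, the same in both arms, and the results that must be in hand. Confirm ineligibility and remove identifiers only after it closes. The sponsor should set its length with section 3b's own range for TB diagnosis in view.
- Report non-enrolled subjects by arm, with counts, characteristics and reasons.
- Reconcile sections 8f iv and 8f v so that one retention rule applies to all randomized subjects.

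The cost is a change to protocol and consent wording and an ethics notification. No new data are collected and the sample size is unchanged. The downside is that coded data on consenting people who were not enrolled are held longer.

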#### *8f v. Destruction of data*

Data will be retained in secure study databases for 7 years following the completion of the study, including completion of all data analysis and report writing associated with the study and closing of the IRB-approved protocol. Study data sets and other electronic files containing study data will then be deleted from electronic storage locations and hard copies of study documents will be shredded.

### **9. Staff Supervision and Training**

The study will be implemented by a Johannesburg-based team employed by the Health Economics and Epidemiology Research Office (HERO), a division of the School of Clinical Medicine at the University of the Witwatersrand. HERO has collaborated closely with the Principal Investigator and other Boston University co-investigators for nearly ten years and completed numerous studies of relevance to the RapIT study.

The local study team will be trained and supervised by the Principal Investigator for HERO. The local team will include a study nurse with responsibility for implementation of all study procedures at the site, one or two study assistants, a data capturer, and a data manager. The study nurse will have the training and qualifications required to initiate ART and be authorized to do so under South African guidelines. Study assistants, who will administer the questionnaire and deliver educational sessions on treatment and wellness, will also be trained as HIV pre- and post-test and ART adherence counselors.

All members of the study team will be trained in and adhere to the standards laid out in the Belmont Report and NIH guidelines for research and in research ethics applicable to South Africa. Human subjects ethics training will be repeated on an annual basis to ensure that the study team's understanding of research ethics is current.

## 10. Sample Size

Track 1: In a recent study we conducted in Johannesburg, we found that among patients eligible for ART, 46% initiated ART within 16 weeks of eligibility. In an analysis of data from the same Johannesburg site, we estimated that among more than 3000 patients initiated on ART in 2010 and 2011 who remained in care, 77% were virally suppressed at the routine 6-month viral load. We would thus expect approximately  $0.46 \times 0.77 = 35\%$  of those eligible to have both started treatment and be virally suppressed by the 6-month viral load. For our study site we conservatively estimate that 50% of those eligible for treatment in the standard group will be suppressed by 10 months after their HIV test. We anticipate that the rapid initiation strategy will increase the proportion suppressed to 70%.

For our primary analysis, using an  $\alpha$  of 0.05, power of 90%, 1:1 randomization, and an uncorrected Fisher's exact test, we would need to enroll 124 HIV positive ART-eligible subjects per group (248 total). We expect 70% of all HIV-positive patients to be eligible for ART under current South African guidelines on the day they test positive for HIV or make their first HIV care visit, based on results from published studies in South Africa. Therefore to reach 124 subjects per arm who are treatment eligible on the day of testing we will need to consent 177 subjects per group (354 total). To allow stratification in the analysis by sex and by site, we will consent up to 300 per group (600 total) to have adequate power. We will enroll in the study up to 67% of this total (enrollment=400).

The sample size for the Track 1 retrospective comparison group will be 120. This group will be limited to patients already found to be eligible for ART at one of the two study sites (Thuthukani). They will be compared with each of the two randomized prospective groups (rapid and standard). We expect that Thuthukani will account for approximately 60% of total prospective enrollment of 400, or 120 in each of the randomized prospective groups. We will thus aim to enroll the same the number of subjects into the retrospective comparison group as in each prospective group.

Track 2: In a study we recently conducted among pregnant women eligible for ART on the day of testing positive for HIV at a different site in Johannesburg, South Africa, we found that 77% of those who initiated ART prior to delivery returned for at least one clinic visit post delivery, which that study used as a proxy to indicate retention on ART through delivery. We believe that an improvement of 25%--i.e., an increase in retention through delivery from 77% to 96%--would be operationally meaningful.

For our primary analysis, using an  $\alpha$  of 0.05, power of 90%, 1:1 allocation of prospective and retrospective subjects, and an uncorrected Fisher's exact test, we would need to enroll 76 HIV positive ART-eligible subjects per group (152 total). If the rate of enrollment allows, we will enroll up to twice this many subjects (305 total) to allow the analysis to be stratified by starting CD4 count, which was previously a criterion for treatment initiation in pregnant women.

Pilot: The first 20 subjects consented for the study in Track 1 and the first 5 subjects consented in the prospective group of Track 2 will serve as a pilot phase to ensure that study procedures run smoothly and confirm that study staff are fully trained. Subjects in the pilot phase will receive the same study procedures as described above for their track and group, and their

data will be included in the analysis. Pilot subjects will be included in the enrollment totals for each track.

The total sample size for the study will therefore be 905 screened and 705 enrolled, as shown below:

| Track        | Total screened | Consented  | Record review only | Screened and not enrolled (not eligible for ART) | Enrolled   |
|--------------|----------------|------------|--------------------|--------------------------------------------------|------------|
| Track 1      | 720            | 600        | 120                | 200                                              | 520        |
| Track 2      | 305            | 153        | 152                | 0                                                | 305        |
| Pilot phase  | n.a.           | n.a.       | n.a.               | n.a.                                             | n.a.       |
| Total | 905     | 753 | 152         | 200                                       | 825 |

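### Section 10 misstates its own figures: totals that leave out 120 subjects, a test that does not match the 124 per group, and an undefined claim of adequate power for strata

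*Protocol*

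**What the plan says.** All of this is in Protocol section 10.

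- **Track 1 size.** The standard-group rate is set by "we conservatively estimate that 50% of those eligible for treatment in the standard group will be suppressed by 10 months", and the rapid-group rate by "We anticipate that the rapid initiation strategy will increase the proportion suppressed to 70" percent. The design is an alpha "of 0.05, power of 90%, 1:1 randomization, and an uncorrected Fisher's exact test". The result is given as "exact test, we would need to enroll 124 HIV positive ART-eligible subjects per group (248 total").
- **Increase for strata.** Stratification is to be "by sex and by site, we will consent up to 300 per group (600 total) to have adequate power", followed by "We will enroll in the study up to 67% of this total (enrollment=400"). The section expects about 60% of the 400 at Thuthukani, which it gives as 120 per randomised group. It adds a Track 1 retrospective comparison group of 120, also from Thuthukani.
- **Track 2 size.** For 77% versus 96%, with the same alpha, power and test label, it gives "exact test, we would need to enroll 76 HIV positive ART-eligible subjects per group (152 total").
- **Overall totals.** "The total sample size for the study will therefore be 905 screened and 705 enrolled, as shown below". The table's Total row then reads 905 screened, 753 consented, 152 record review, 200 not enrolled and 825 enrolled.

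**The concern.** A reader should be able to take three things from this section: how many people the study covers, what power the stated sizes give and with which test, and what can be expected of the results by site and sex. Each is compromised.

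The enrolled total differs by 120 between one sentence and the table it introduces. The 120 in question are the record-review group enrolled without consent, so the count ought to be unambiguous.

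The test label names a procedure that does not give the stated power at the stated size. The word uncorrected belongs to a chi-square test, not to Fisher's.

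The increase from 248 to 400 is justified by a power claim that cannot be checked as worded. On the section's own site split it is doubtful for the smaller site.

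**Working it through.** **1. Totals**

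| | Screened | Consented | Record review | Not enrolled | Enrolled |
|---|---|---|---|---|---|
| Track 1 row | 720 | 600 | 120 | 200 | 520 |
| Track 2 row | 305 | 153 | 152 | 0 | 305 |
| Sum of rows | 1,025 | 753 | 272 | 200 | 825 |
| Printed Total row | 905 | 753 | 152 | 200 | 825 |
| Text | 905 | – | – | – | 705 |

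The gaps are 1,025 − 905 = 120, 272 − 152 = 120 and 825 − 705 = 120. The text's figures equal 600 + 305 = 905 and 400 + 305 = 705, that is, Track 1 without its retrospective group. The printed Total row is also inconsistent within itself: 905 − 200 = 705, not 825. With the corrected figure, 1,025 − 200 = 825. The printed 753, 200 and 825 are right.

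**2. Track 1 size and test**

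Inputs: p1 = 0.50, p2 = 0.70, alpha 0.05 (two-sided assumed, since the section does not say), power 90%, 1:1 allocation.

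Uncorrected normal-approximation (chi-square) formula, with mean rate p̄ = 0.60:

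n = [1.960 √(2 p̄(1 − p̄)) + 1.2816 √(p1(1 − p1) + p2(1 − p2))]² / (p2 − p1)²

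= [1.960 √0.48 + 1.2816 √0.46]² / 0.04 = (1.3579 + 0.8692)² / 0.04 = 124.0.

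So the plan's 124 reproduces exactly, and 124 / 0.70 = 177 also reproduces its consent target.

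Power of the two-sided Fisher's exact test, by full enumeration of the two binomials at 50% and 70%:

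| Per group | Fisher power |
|---|---|
| 124 | 87.3% |
| 132 | 89.8% |
| 133 | 90.1% |
| 200 (planned) | 98.0% |

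At 200 per group the chi-square approximation gives 98.5%.

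**3. Track 2 size**

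The same uncorrected formula at 77% versus 96% gives (0.9472 + 0.5949)² / 0.19² = 65.9, or 66 per group. The stated 76 does not follow from that. Two other routes come close:

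- With a continuity correction at 77% versus 96%: 76.04, which rounds up to 77.
- Uncorrected at 77% versus 95%: (0.9618 + 0.6074)² / 0.18² = 75.99, which rounds up to 76.

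The document does not show which was used, if either. Fisher power at 76 per group for 77% versus 96% is 93.2%.

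**4. Strata at 400 enrolled**

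Site split from section 10: 0.60 × 200 = 120 per group at Thuthukani, leaving 200 − 120 = 80 per group at the other site. No split by sex is given, so equal halves (100 per group) are an assumption. Approximate power is Φ[(0.20 √n − 1.3579) / √0.46].

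| Stratum | Per group | Chi-square approximation | Fisher, enumerated |
|---|---|---|---|
| Larger site | 120 | 89.0% | 86.9% |
| Smaller site | 80 | 73.7% | 67.7% |
| Each sex, if equal | 100 | 82.8% | 79.2% |

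An unequal sex split would lower the power in the smaller sex stratum.

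**The case against.** The strongest reply is that none of this harms the main comparison. That stands: with up to 400 enrolled, power is about 98% by either test. Section 11b describes crude risk ratios with confidence intervals rather than Fisher's test, so 87.3% describes neither the planned size nor the described analysis. The fault is a mislabelled calculation, not an underpowered trial.

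The totals error can fairly be called clerical. Every correct component is visible in the table, and no analysis depends on the Total row. It would also be too broad to say that the table leaves out the 120, because its Track 1 row and its enrolled total of 825 include them. But the text and the table still contradict each other on how many are enrolled.

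On strata, a reader might infer that two strata at 124 per group require 2 × 248 = 496 enrolled, so that 400 is short. The document does not support this. The 90% is attached to the primary analysis. No power or effect is set for strata, and section 11b sets out no site- or sex-specific test for Track 1. What stands is that the adequacy claim is undefined and that the smaller site falls below even a conventional 80%. That figure rests on a forecast of about 60% at one site.

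On Track 2, a reader might infer that 76 came from a continuity correction. That is not established, since a one-point change in the target rate reproduces 76 without one.

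**Conclusion.** The point holds as errors of statement in section 10.

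- **Totals.** Certain, with no assumption needed: 905, 152 and 705 should be 1,025, 272 and 825.
- **Track 1 test.** Given a two-sided alpha of 0.05, 124 is the uncorrected chi-square size. Fisher's test as named has 87.3% power there and needs 133 per group (266 in total). The planned enrolment removes any practical effect.
- **Track 2 size.** The stated inputs and label give 66, not 76. The origin of 76 is unknown, and the size is sufficient for the stated effect.
- **Strata.** If the 50% versus 70% effect held in each stratum and the 60:40 split were realised, power would be 87–89% at the larger site and 68–74% at the smaller. Equal sexes would give 79–83%. The claim of adequacy is undefined and, for the smaller site, not borne out.

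**What to change.** 1. In the table's Total row, print 1,025 screened, 753 consented, 272 record review, 200 not enrolled and 825 enrolled. In the text, print 1,025 screened and 825 enrolled.
2. For Track 1, name the uncorrected chi-square test as the basis of 124 per group, or keep Fisher's exact test and state 133. Give the sidedness of alpha, and note that 200 per group has about 98% power.
3. For Track 2, the sponsor should check how 76 was obtained and state the method or inputs.
4. Replace the claim of adequate power for stratification with the stratum powers above and their assumptions, and describe results by site and by sex as exploratory.

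The cost is wording only: no added patients and no change of design. The stated stratum power becomes less favourable than the present text implies.
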